### Interventions

In both study groups, the TOP will be determined: first, participants will be asked to remain at rest in the supine position for 10 min in an acclimatized room (21–23°C) and silent [43, 44]. To determine the TOP, a vascular Doppler (DF-7000 V; Medpej, Ribeirão Preto, São Paulo, Brazil) will be used, which will be positioned over the posterior tibial artery (located in the middle distance between the medial malleolus of the tibia and the Achilles tendon) to capture the auscultatory pulse [45].

A cuff (velcro; 12.5 cm wide and 84 cm long and inflatable chamber 7 cm wide and 52 cm long, Cardiomed, Curitiba, Paraná, Brazil) will be positioned in the region of the inguinal fold with the inflatable region of the cuff in the medial portion of the thigh covering the femoral artery [46] of the lower limb with the greatest complaint of knee pain [45, 46] and then it will be progressively inflated waiting 30 s every 50 mmHg and completely deflating and pausing for 10 s, and 40 mmHg will be added to the initial 50 mmHg (total of 90 mmHg).

The sequence will be repeated, always adding the 40 mmHg until the auscultatory pulse of the tibial artery is completely interrupted. Then wait 30 s and slowly deflate until the auscultatory pulse returns. The TOP will be defined when the lowest pressure capable of completely obstructing blood flow is reached [45, 47–49]. A wider cuff was chosen, as it has been proven that the width of the cuff has a great influence on the pressure needed to achieve full restriction of blood flow [49]. The intervention and placebo groups will be different as described below.

### Remote ischemic conditioning

The RIC protocol will be applied to the proximal region of the thigh of the limb with knee osteoarthritis and if both knees are affected, it will be applied to the knee with the greatest pain complaint [33]. Participants will be relaxed and comfortably positioned in the supine position. The same cuff used to determine TOP will be used and the protocol will consist of four cycles of total ischemia (according to the TOP value determined individually) of 5 min, followed immediately by four cycles of 5 min of vascular reperfusion (0 mmHg), totaling 40 min as shown in Fig. 3.

**Fig. 3 Fig3:**
[figure not shown]
RIC and P-RIC protocol

### Placebo remote ischemic conditioning

The placebo RIC protocol will also be performed on the lower limb with knee osteoarthritis and if both knees are affected, it will be applied on the knee with the greatest pain complaint. Participants will perform a protocol similar to that of RIC, but during the four cycles of 5 min of occlusion, the cuffs will be inflated only with 10 mmHg so as not to cause arterial or venous occlusion alternating with four cycles of 5 min of reperfusion (0 mmHg) (see Fig. 3) [50, 51].

### Outcomes

#### Conditioned pain modulation

CPM is a dynamic measure capable of evaluating endogenous pain inhibition using a “pain-by-pain inhibition” model in which pain in a local area (test stimulus) is inhibited by a second concomitant pain (conditioning stimulus) [3, 52]. In this study, the test stimulus will be performed through the pressure pain threshold using the algometer, and the conditioning stimulus will be performed through the immersion of the hand in cold water, using the cold pressor test (CPT).

First, the markings of the places where the test stimuli will be performed on the participant will be carried out. The participant will be in dorsal decubitus with approximately 20° of hip and knee flexion with the lower limb comfortably supported and markings will be performed in eight locations on both knees: site 1: 2 cm distal to the lower medial border of the patella; site 2: 2 cm distal to the lower lateral border of the patella; site 3: 3 cm lateral to the midpoint on the lateral edge of the patella; site 4: 2 cm proximal to the upper lateral border of the patella; site 5: 2 cm proximal to the upper edge of the patella; site 6: 2 cm proximal to the upper medial border of the patella; site 7: 3 cm medial to the midpoint on the medial border of the patella; site 8: in the center of the patella [53, 54] and in the joint space between the first and second metacarpophalangeal joints (thenar eminence region of the hand) on the contralateral side [33].

These marked sites will receive the test stimulus through the pressure pain threshold test using a pressure algometer which is a reliable and validated instrument (FDX 50/220; Wagner instruments, Greenwich, Connecticut, USA) which has a tip of 1 cm^2^ [55].

The evaluator will apply pressure perpendicularly to the participant’s skin until she reports the change from pressure sensation to painful sensation [33]. The procedure will be performed three times at each site and the mean values in kgf/cm^2^ will be calculated to determine the pressure pain threshold. An interval of 20 s will be maintained between applications to avoid sensitization of pain responses [33].

After each measurement of the pressure pain threshold, pain will be asked using a visual analog scale (VAS) that ranges from 0 (no pain) to 100 (worst imaginable pain). VAS will also be used to measure knee pain at rest and during CPT [5, 33, 54].

After baseline pressure pain threshold measurements, the CPT (conditioning stimulus) [5, 33, 56] will be applied. Participants will be asked to dip their hands in a container of cold water and ice for up to 1 min. The temperature will be monitored by a thermometer (model 5130, Incoterm) and maintained between 1°C and 4°C [33]. Soon after, the pressure pain threshold measurements (test stimulus) will be performed in the same places.

MCD will be quantified by subtracting the second mean pressure pain threshold value (after CPT) from the first mean pressure pain threshold value (before CPT) [CPM = baseline pressure pain threshold − pressure pain threshold Final]. Thus, negative CPM values mean CPM inhibitory activity (higher pressure pain threshold after CPT), while positive values indicate CPM facilitating activity (lower pressure pain threshold after CPT) [3, 33, 56]. The percentage of change will also be calculated using the following formula: [(pain threshold at final pressure − pain threshold at baseline pressure)/pain threshold at final pressure) × 100]. This entire protocol will be repeated after the RIC (Fig. 4) [53].

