**Methods:**

Women more than 50 years with knee osteoarthritis diagnosed according to the American College of Rheumatology criteria in the postmenopausal period will be considered eligible. The study will have blind randomization, be placebo-controlled, and be balanced in a 1:1 ratio. The total of 44 participants will be divided into two groups (22 participants per group): (i) remote ischemic conditioning and (ii) placebo remote ischemic conditioning. Protocol consisting of four cycles of total ischemia, followed immediately by four cycles of 5 min of vascular reperfusion, totaling 40 min. The primary outcomes in the protocol are conditioned pain modulation, which has the pressure pain threshold (kgf/cm^2^) as its primary outcome measure, and cardiac autonomic modulation, which has the indices found in heart rate variability as its primary outcome measure. Comparisons will be performed using generalized linear mixed models fitted to the data. For correlation, the Pearson or Spearman test will be used depending on the normality of the data. All analyses will assume a significance level of *p* < 0.05.

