### Sample size

The sample size calculation was based on the study by Schliessbach et al. [66], using the CPM test variable. The software G*Power 3.1.9.4 and a reference value of 98 ± 103 kPa were used, using a two-tailed hypothesis test with a test power of 80% and a significance level of 5%. Eventually, 19 participants per group were stipulated. A possible sample loss of 15% was considered so three participants will be added to each group, totaling 44 individuals divided into two groups (22 participants per group).

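### The supplementary percentage change in CPM is divided by the post-conditioning threshold instead of baseline, and its sign is opposite to the absolute CPM score with no sign rule given

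*Protocol article*

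**What the plan says.** The Protocol article, under Conditioned pain modulation, gives two expressions of CPM, both built from the mean PPT before and after the cold pressor test.

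- **Absolute score:** "CPM = baseline pressure pain threshold − pressure pain threshold Final". Its sign is explained in words: "negative CPM values mean CPM inhibitory activity (higher pressure pain threshold after CPT", and positive values mean facilitation.
- **Percentage:** it is introduced as an addition, "The percentage of change will also be calculated using the following formula". The numerator is "pain threshold at final pressure − pain threshold at baseline pressure" and the denominator is the final threshold: "pain threshold at baseline pressure)/pain threshold at final pressure) × 100".

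Both apply twice per participant, since "This entire protocol will be repeated after the RIC". The article gives no reason for dividing by the final value and no interpretation of the percentage's sign. No other section restates or corrects the formula.

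The abstract names as a primary outcome "conditioned pain modulation, which has the pressure pain threshold (kgf/cm^2^) as its primary outcome measure", an absolute unit. The Sample size section also works in absolute units: "a reference value of 98 ± 103 kPa were used". The Statistical analysis section plans mixed models, Cohen's d and a correlation of CPM with cardiac autonomic modulation, without saying which expression of CPM enters each.

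**The concern.** There are two separate problems in one line.

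The first is the denominator. The article itself labels the first threshold as baseline, so a percentage change should be relative to it. Dividing by the post-conditioning value is not a harmless rescaling. It treats rises and falls asymmetrically, so a group mean can shift and even change sign, and a contrast between arms changes size. The resulting figures could not be set directly beside percentage changes from baseline reported elsewhere.

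The second is the sign. The only sign rule in the article (negative means inhibition) belongs to the absolute score. A reader who applies it to the percentage will read inhibition as facilitation. As the analysis section does not say which score is correlated with the heart rate variability indices, the direction of that correlation would be expected to depend on an unstated choice.

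**Working it through.** **Inputs from the article.** Absolute score = B - F. Percentage = 100(F - B)/F. Here B is mean PPT before and F mean PPT after the cold pressor test. The article gives no baseline PPT and no expected percentage, so the thresholds and percentages below are illustrative assumptions.

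**The plan's own figure.** No numerical percentage is printed, so there is none to reproduce. The only related figure is the sample size. With the stated 98 and 103 kPa, d = 98/103 = 0.951. A two-sided two-sample t-test at 5% with 80% power needs 18.35, so 19 per group as stated. Adding 15%, 19 × 1.15 = 21.85, so 22 as stated. The percentage formula does not enter this calculation.

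**Denominator.** Let r = F/B. The written formula gives 100(1 - 1/r). Change from baseline is 100(r - 1). The ratio alone determines both, so the assumed B = 4 kgf/cm² does not matter for the percentages.

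| B | F | Absolute, B - F | As written, (F - B)/F | From baseline, (F - B)/B |
|---|---|---|---|---|
| 4 | 2 | +2 | -100.0% | -50.0% |
| 4 | 3 | +1 | -33.3% | -25.0% |
| 4 | 3.6 | +0.4 | -11.1% | -10.0% |
| 4 | 4 | 0 | 0% | 0% |
| 4 | 4.4 | -0.4 | +9.1% | +10.0% |
| 4 | 5 | -1 | +20.0% | +25.0% |
| 4 | 6 | -2 | +33.3% | +50.0% |
| 4 | 8 | -4 | +50.0% | +100.0% |

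As r grows, 1 - 1/r approaches but never reaches 1, hence the cap below +100%. As r approaches 0 it falls without limit.

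**Means.** Two participants at +25% and -25% from baseline average 0. As written they are +20.0% and -33.3%, mean -6.7%. At +30% and -20% the mean from baseline is +5%; as written, 1 - 1/1.3 = +23.1% and 1 - 1/0.8 = -25.0%, mean -1.0%. The sign of the group mean is reversed.

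**Contrasts between arms.** For two arms with ratios r1 and r2, the written contrast is 1/r1 - 1/r2 = (r2 - r1)/(r1 r2). The contrast from baseline is therefore divided by r1 r2.

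- Both rise, +10% and +50%: 40 points becomes 40/(1.1 × 1.5) = 24.2.
- Both rise, +20% and +60%: 40 becomes 40/(1.2 × 1.6) = 20.8.
- Mixed, -20% and +20%: 40 becomes 40/(0.8 × 1.2) = 41.7.
- Both fall, -10% and -40%: 30 becomes 30/(0.9 × 0.6) = 55.6.

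**Sign.** In every row with a non-zero change, the third and fourth columns have opposite signs. So do the third and fifth: correcting the denominator alone leaves the sign conflict, because it comes from the reversed order of subtraction.

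**The case against.** The strongest reply is about reach. The percentage is only an additional expression. The primary measure is PPT in kgf/cm², the absolute score is defined consistently with an explicit sign rule, the sample size uses absolute units, the planned analyses never name the percentage, and the trial is described as exploratory. All of this stands. A reader might infer that the primary outcome is computed wrongly; the article does not support that.

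A reader might also infer that every reported percentage is wrong, or that the formula always hides a treatment effect. Neither follows. Zero stays zero and small changes barely move (+10% becomes +9.1%). The contrast shrinks when both arms rise, but grows when both fall. The introduction describes osteoarthritis patients as having less efficient inhibition, so falls cannot be ruled out. A smaller contrast in points also does not show lost sensitivity, because the standard deviation changes scale as well.

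The formula is strictly increasing in r, so for a single percentage at one site the ranking of participants, and hence a Spearman correlation, is unchanged by the denominator. This also stands, but it is narrow. It does not extend to means, Pearson correlations or model estimates. Nor need it hold for the change between the two CPM tests: +10% to +50% (40 points) and -10% to +20% (30 points) become 24.2 and 16.7 + 11.1 = 27.8, which reverses their order.

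On the sign, final minus baseline is the ordinary direction for a percentage change and neither statement is false in itself. That is fair: the sign problem is one of clarity, and the cited absolute definition need not be altered.

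Finally, the unbalanced brackets in the printed formula are compatible with a typesetting slip. That cannot be settled from the article, and anyone following the text would still compute the wrong figure.

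**Conclusion.** The point holds for the supplementary percentage. The stated formula does not give a percentage change from baseline. The error is negligible for small changes and large for big ones: +50% is reported as +33.3%, +100% as +50%, and -50% as -100%. Mean percentages and contrasts between arms are distorted, in a direction that depends on whether thresholds rise or fall. Separately, for every non-zero change the percentage has the opposite sign to the absolute score, and the article gives no rule for reading it.

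The algebra needs no assumption. The sizes quoted are illustrative, because the article reports no thresholds or expected percentages. The absolute CPM score, the PPT and the sample size of 19 (22 with loss) per group are not affected. Nothing is irreversible either: each individual value can be recomputed from the raw thresholds, which the article says will be kept.

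**What to change.** 1. Replace the percentage formula with 100 × (final PPT - baseline PPT)/baseline PPT, with the brackets balanced.
2. Settle the sign. Either use one convention for both scores, or keep the absolute definition as it is and add a sentence that a positive percentage means inhibition while a negative absolute score means inhibition. This second edit is needed even after the first.
3. Where CPM is correlated with the heart rate variability indices, say which score is used, so that the direction of the coefficient can be read.

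The cost is a line or two of wording. No measurement, visit or sample size changes. The Trial status section says recruitment had not begun, so the correction can be made before any data exist and would not look like a post hoc redefinition.

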**Fig. 4 Fig4:**
[figure not shown]
Pressure pain threshold measurement sites [53]

#### Cardiac autonomic modulation

The collection of data will be carried out individually and the participants will be instructed to remain silent, awake, at rest, and in the supine position. The movement of people on site will be restricted, in order to reduce interference during collection. Participants will be instructed not to consume ANS stimulant substances such as alcoholic beverages, coffee, tea, soft drinks, and chocolate drinks during the 24 h prior to capturing the RR intervals.

The assessment of cardiac autonomic modulation will be performed through HRV by capturing the RR intervals using the heart rate monitor (Polar Electro Oy, Kempele, Finland – model V800) which is a validated equipment [57].

Indices obtained through linear methods, in the time domain (Mean RR, SDNN, and rMSSD), frequency (LF and HF), and the Poincaré plot (SD1 and SD2) will be analyzed [58, 59]. In addition, RR intervals will be analyzed to obtain the 30s rMSSD that represents vagal reentry. All HRV indices will be obtained using the software Kubios HRV – version 3.2 (The Biomedical Signal Analysis Group, Department of Applied Physics, University of Kuopio, Finland) [60].

For this analysis, the time series of RR intervals will be initially submitted to a digital filtering moderated by the software Kubios HRV – version 3.2 [60] complemented by manual filtering, to eliminate premature ectopic beats and artifacts, and only series with more than 95% of sinus beats will be included in the study [58]. Through the visual analysis of the time series, the absence of artifacts or ectopic beats that may interfere with the HRV analysis will be observed.

The series of RR intervals will be analyzed in two different moments: (i) during the performance of the CPM tests and (ii) during the evaluation of the RIC. In order to obtain these analyses, on the first day of the intervention, the following moments will be analyzed: M1 (10 min basal at rest before TOP), M2 (test stimuli through the algometer), M3 (conditioning stimulus, through the CPT), M4 (test stimuli through the algometer), M5 (during RIC), M6 (test stimuli through the algometer), M7 (conditioning stimulus, through the CPT), M8 (test stimuli through the algometer). In these stretches, 256 consecutive RR intervals [59] will be obtained. It is worth noting that at moments M3 and M7, only vagal reentry with a rMSSD of 30 s will be analyzed due to the short time to capture the RR intervals.

On the second day of the intervention, the Pre-RIC (15 min baseline before RIC), RIC (during RIC), and Post-RIC (15 min after RIC) moments will be analyzed, with 1000 consecutive RR intervals being obtained for this analysis [59].

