### Study design

Data collection will be carried out at Sports Physiotherapy Laboratory at São Paulo State University (Unesp), School of Technology and Sciences, Presidente Prudente, São Paulo, Brazil. All procedures will be performed under standardized conditions (temperature: 21–23°C; relative humidity: 40–60%).

Each participant will attend the laboratory on two days separated by one week. On the first day they will be evaluated for anthropometric characteristics, using a scale (Tanita BC 554, Iron Man/Inner, Arlington Heights Illinois, USA) and a stadiometer (Sany—American Medical do Brasil, São Paulo, Brazil) and, later, the body mass index (BMI) will be calculated. Blood pressure measurements will also be performed [41] and the Knee Injury and Osteoarthritis Outcome Score (KOOS) questionnaire [42] will be applied. After these initial procedures, a 10 min rest will be performed and, in the sequence, the evaluation of total occlusion pressure (TOP) will be performed. After that, the initial CPM test will be performed, followed by the RIC, and finally the CPM test again. RR intervals will be captured from the initial 10 min of rest to the end of the complete CPM protocol.

On the second day, only the RR intervals will be captured before the RIC (15 min at rest), during, and after (15min at the end) the RIC. The study design is outlined in Fig. 2.

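### The only pre-intervention CPM test follows a full occlusion of the painful limb with no stated rest, so within-arm CPM changes do not start from an unexposed state; the between-arm contrast is not biased.

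*Protocol article*

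**What the plan says.** Study design (Protocol article) gives the day-1 order. After the initial measurements, "a 10 min rest will be performed and, in the sequence, the evaluation of total occlusion pressure (TOP) will be performed". It then continues: "After that, the initial CPM test will be performed, followed by the RIC, and finally the CPM test again". The list of moments under Cardiac autonomic modulation agrees with this: "M1 (10 min basal at rest before TOP), M2 (test stimuli through the algometer", followed by cold water (M3) and a second threshold series (M4). CPM1 is thus formed from M2 to M4, after TOP, and the resting HRV baseline M1 comes before it.

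Interventions describes TOP. "In both study groups, the TOP will be determined", with the cuff on the thigh "of the lower limb with the greatest complaint of knee pain". Inflation starts at 50 mmHg, each step is held 30 s and fully released, and the pressure then rises: "The sequence will be repeated, always adding the 40 mmHg until the auscultatory pulse of the tibial artery is completely interrupted". Occlusion is held for another 30 s before a slow deflation. The RIC arm then receives four 5-min occlusions with the same cuff. The placebo arm receives 10 mmHg, set "so as not to cause arterial or venous occlusion".

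Statistical analysis compares outcomes between groups and between moments with mixed models and Bonferroni post-tests, and correlates CPM with cardiac autonomic modulation.

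**The concern.** CPM is a primary outcome, and CPM1 is its only pre-intervention measurement. It is taken after every participant, placebo included, has had a real arterial occlusion on the limb that carries about half of the pressure sites. A 10-min rest is specified before TOP, but none is stated after it.

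CPM is a difference between the threshold series before and after cold water. An after-effect of TOP that fades with time would weigh more on M2 than on M4. It would therefore not cancel within CPM1, and would be weaker or absent at CPM2. The CPM1-to-CPM2 change in either arm could then partly reflect recovery from TOP rather than RIC or sham. Because moments are compared as well as groups, such a change could be reported as a finding.

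**Working it through.** **1. Order of events.** Study design and Cardiac autonomic modulation give the same sequence: rest (M1), TOP, CPM1 (M2–M4), allocated intervention (M5), CPM2 (M6–M8). No rest appears between TOP and M2.

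**2. The plan's own figure.** Sample size uses 98 ± 103 kPa, two-sided 5%, 80% power. d = 98/103 = 0.951. The two-sample t test needs 18.35, so 19 per group, with power 0.814. The stated 19 is reproduced. The timing point does not depend on it.

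**3. Exposure.**
- Full occlusion in TOP lasts about 30 s, or up to about 60 s if the final step's own 30 s is counted. RIC gives 4 × 5 = 20 min = 1,200 s. The ratio is 30/1,200 = 2.5% to 60/1,200 = 5%.
- For an assumed TOP of 130 to 250 mmHg (not given), steps of 50, 90, 130 … mmHg give 3 to 6 inflations, that is 90 to 180 s under the cuff.
- Reading the sites as eight per knee plus one hand gives 17. A series takes about 17 × 3 × 20 s = 1,020 s = 17 min. Eight of the 17 sites are on the cuffed limb.

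**4. Between-arm contrast.** Let TOP shift CPM1 by t in both arms. The change is (effect − t) under RIC and (0 − t) under placebo, and t cancels in the difference. A simulation (19 per arm, SD 103, assumed CPM1–CPM2 correlation 0.5, true effect 98) gives, rounded:

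| t (kPa) | RIC change | Placebo change | Difference | Power |
|---|---|---|---|---|
| 0 | 98 | 0 | 98 | 0.81 |
| 30 | 68 | −30 | 98 | 0.81 |
| 60 | 38 | −60 | 98 | 0.81 |

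**5. Within-arm comparison.** Paired t test in the placebo arm, n = 22. With correlation 0.5 the SD of change is 103 × √(2 × (1 − 0.5)) = 103. Noncentrality is √22 × t/103.

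| Assumed t (kPa) | Chance of p < 0.05 |
|---|---|
| 2.45 (2.5% of 98) | 5.1% |
| 4.9 (5% of 98) | 5.5% |
| 20 | 14% |
| 30 | 26% |
| 49 (50% of 98) | 57% |

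The first two rows assume a shift proportional to occlusion time. Bonferroni adjustment would lower all of these.

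**6. Noise in CPM1.** Let the TOP response vary between women with SD s (assumed), 19 per arm, difference 98. For the unadjusted change, SD = √(103² + s²). With baseline adjustment, SD = 103 × √(1 − r²), where r = 0.5 × 103/√(103² + s²).

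| s (kPa) | SD, change | Power, change | SD, adjusted | Power, adjusted |
|---|---|---|---|---|
| 0 | 103.0 | 81% | 89.2 | 91% |
| 30 | 107.3 | 78% | 90.4 | 90% |
| 50 | 114.5 | 73% | 92.0 | 89% |
| 70 | 124.5 | 66% | 93.8 | 88% |

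A comparison of CPM2 alone does not use CPM1 and stays at 81%.

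**The case against.** A reader might infer that TOP spoils every before/after-RIC comparison of CPM. The document does not support this. TOP is applied identically to both randomised arms before they diverge, so a common shift leaves the group-by-moment contrast and its power unchanged. Dilution would require TOP itself to use up part of the RIC effect, and nothing in the document shows that.

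The size of any after-effect is also open. No section says that TOP changes pressure pain thresholds, and the adverse-event section says that cuff discomfort and tightness disappear once pressure is removed. The larger assumed shifts are demanding: if the effect is local and the sites are averaged (both assumptions), a mean shift of 49 kPa needs 49 × 17/8 ≈ 104 kPa at the exposed sites, more than the 98 kPa used for sizing. An effect that fades within about 17 min would also fade during M2 itself. These points stand and limit the size of the concern.

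Some interval after TOP must exist, since the sites are marked and the leg is positioned first, and a condensed article may omit a pause. So it cannot be said that M2 begins within seconds, only that no rest is stated.

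A reader might also infer that the CPM–HRV correlation is distorted because M1 precedes TOP. The plan does not say that CPM1 is paired with M1, and HRV is also recorded at M2 to M4, in the same post-TOP state as CPM1.

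What the objection does not remove is that comparisons between moments are planned and that their only CPM baseline follows a real occlusion in both arms.

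**Conclusion.** The point holds in a limited form. CPM1 is a post-occlusion measurement with no stated rest before it, whereas M1 is a pre-occlusion one. Within-arm CPM changes, including the placebo arm's, therefore cannot be read as change from an unexposed state. The randomised RIC-versus-placebo contrast is not biased.

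The within-arm effect ranges from negligible (about 5% of trials significant, the nominal level) under a shift proportional to occlusion time to substantial (57%) under a shift of half the effect sized for. These figures rest on an assumed shift and an assumed correlation of 0.5. Extra variation costs up to 15 percentage points of power (81% to 66%) for an unadjusted change score, but about 3 points (91% to 88%) with baseline adjustment. The change is worth making because it protects the sole baseline of a primary outcome cheaply, and the article states that recruitment had not begun.

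**What to change.** Keep the order of procedures and insert a stated rest between TOP and M2, for example 10 min to match the rest already specified before TOP. State that the conclusion about RIC rests on the between-arm contrast, preferably adjusted for CPM1, and that within-arm changes between moments are descriptive.

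The cost is about 10 min more in the day-1 session, with no change to cuff settings or equipment. A rest removes only short-lived after-effects.

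Moving TOP to after M4 would give CPM a pre-occlusion baseline, but it is not recommended without further thought. It would place real occlusion between CPM1 and CPM2 in the placebo arm. It would also conflict with the supine rest specified before TOP, which would follow painful pressure and cold-water immersion unless another rest were added.

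### Day 2 heart rate variability: 1000 consecutive RR intervals cannot be obtained from a 15-min rest recording when mean heart rate is below 66.7 bpm

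*Protocol article*

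**What the plan says.** The Study design section sets the Day 2 recordings: "only the RR intervals will be captured before the RIC (15 min at rest), during, and after (15min at the end) the RIC". The Cardiac autonomic modulation section repeats the 15-min lengths for Pre-RIC and Post-RIC and adds the series length: "and Post-RIC (15 min after RIC) moments will be analyzed, with 1000 consecutive RR intervals being obtained for this analysis". I read this as 1000 intervals for each of the three Day 2 moments, since each is analysed as a moment of its own.

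The same section has recordings made supine and at rest, with stimulants withheld for 24 h, and adds a quality criterion: "only series with more than 95% of sinus beats will be included in the study". Mean RR is among the listed indices, and the abstract names heart rate variability indices as a primary outcome measure. The eligibility criteria contain no heart-rate limit.

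The Remote ischemic conditioning section gives the procedure as "four cycles of total ischemia (according to the TOP value determined individually) of 5 min, followed immediately by four cycles of 5 min" of reperfusion, 40 min in all. The article does not say where in those 40 min the 1000 intervals are taken.

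**The concern.** A beat count and a recording time are both fixed, and whether they agree depends on heart rate. Resting, supine women without stimulants may well have rates at which 15 min does not contain 1000 beats.

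Three things are at stake:

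- Day 2 holds the only rest recording after RIC. On Day 1 the moments after RIC are taken during algometry and the cold pressor test. The resting before-after comparison of a primary outcome therefore rests on these series.
- Any series that meets the requirement within 15 min must have a Mean RR of 900 ms or less. If it is enforced, it truncates one of the indices it is meant to measure.
- If it is not enforced, slower women contribute shorter series, so the basis of the indices differs by heart rate. The article does not say which of the two happens.

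**Working it through.** **Inputs from the article.** 1000 RR intervals per Day 2 moment; 15 min Pre-RIC and 15 min Post-RIC; RIC phases of 5 min, 40 min in total; 256 intervals per moment and a 10-min baseline on Day 1. The article derives no figure for the 1000-interval requirement and gives no heart rate, so there is nothing of its own to reproduce first.

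**1. Threshold.** Number of intervals = mean heart rate x minutes.

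- Minimum rate: 1000/15 = 66.7 bpm, that is, Mean RR of at most 15 x 60 x 1000/1000 = 900 ms.
- 60 bpm: 60 x 15 = 900. 65 bpm: 975. 66 bpm: 990. 67 bpm: 1005.
- Time needed for 1000 intervals: 1000/60 = 16.7 min at 60 bpm; 1000/50 = 20 min at 50 bpm.
- If filtering removed 5% of beats without replacement (an assumption), the minimum would rise to 1000/(0.95 x 15) = 70.2 bpm.

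**2. Share affected (illustrative).** The mean and SD are my assumptions. With normal resting heart rate, share = Phi((66.7 - mean)/SD).

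| Mean (bpm) | SD 8 | SD 10 |
|---|---|---|
| 65 | 58% | 57% |
| 70 | 34% | 37% |
| 75 | 15% | 20% |
| 80 | 5% | 9% |

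Of 44 women this is about 26 at the top (0.58 x 44) and about 2 at the bottom (0.05 x 44).

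**3. What is not affected.** Day 1 needs 256 intervals: 256/10 = 25.6 bpm for the 10-min baseline. The 30-s rMSSD uses only the last 30 s of each moment. Conditioned pain modulation does not use RR intervals. The 40-min recording during RIC needs only 1000/40 = 25 bpm.

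**4. The window during RIC.** 1000 intervals last 1000/80 = 12.5 min at 80 bpm and 16.7 min at 60 bpm. To stay within one 5-min phase, 1000/5 = 200 bpm would be needed, so the window always spans several phases. The mix depends on where it starts. At 70 bpm it lasts 1000/70 = 14.3 min. Starting with an ischemia phase it holds 5 + 4.3 = 9.3 min of ischemia (65%); starting with reperfusion it holds 5 min (35%).

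**The case against.** The strongest reply is that the article never says a short series is dropped. Its RR-related exclusions are capture errors and series that fail the sinus-beat criterion, and it plans intention to treat with mixed-model imputation. A 900-interval series could simply be analysed, and how short series are handled may be set out in a fuller document. This stands against a reading that slow-hearted participants are lost to the trial, which the text does not support. It does not remove the conflict, because the article itself fixes both numbers. Nor would imputation fully cure discarded series, since the missingness would follow Mean RR itself.

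A reader might also infer that RIC slows the heart, so that the series lost would be those of the best responders. That does not follow. The threshold acts on absolute heart rate and not on change, and the women below it may be mainly those who were slow at baseline in either arm. The stated hypothesis is improved autonomic modulation, not a lower heart rate.

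The size is open to dispute as well. The article excludes beta-blocker users and highly active women and describes sympathetic predominance in chronic pain, which if anything points to faster rates. The lower shares in the table are therefore possible.

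Finally, mixing phases during RIC may look like an error in itself. It is not: the article defines a single moment during RIC, the intervention is the whole alternating sequence, and the placebo follows the same timing. Nor is distortion of LF a strong argument. A 10-min phase cycle is about 0.0017 Hz, while LF starts at 0.04 Hz. An ideal square wave of that period puts only about 1% of its variance in the LF band, roughly 5 of 400 ms² for an assumed 40-ms step (40²/4 = 400).

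**Conclusion.** The conflict is real and follows from the article's own figures: below 66.7 bpm, a 15-min recording cannot yield 1000 intervals. It touches only the Day 2 Pre-RIC and Post-RIC series and the indices computed from them, but these carry the resting before-after comparison for a primary outcome.

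The consequence is one of two things, and the article does not settle which: selective failure by Mean RR, or series lengths that vary with heart rate. How many women are affected cannot be derived from the article; the 5-58% spanned by the table rests wholly on assumed heart-rate distributions. A difference in failure between the arms is possible but not shown.

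For the recording during RIC there are enough beats. What needs settling there is the window's position, because the share of ischemia in it otherwise depends on start point and heart rate.

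This should be fixed, but it does not threaten the trial as a whole.

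**What to change.** For the two Day 2 rest recordings, replace the 1000-interval count by one fixed time window that any 15-min recording can supply, of equal length and position before and after RIC and in both arms. State its position with the acute question in mind: a window confined to the last 10 min, for example, would leave out the first 5 min after RIC.

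For the recording during RIC, define the window as whole ischemia-reperfusion cycles at the same position for every participant, so that each window is half ischemia and half reperfusion. Separate analysis of each phase is an optional refinement.

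The cost is a change of analysis wording; visits and recordings stay as they are. The small downside is that the number of beats will vary with heart rate and the analysis departs from the 1000-beat convention that the article cites. The Trial status section reports that recruitment had not begun, so the change can be made before data collection.
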